### Participants timeline

The study duration for each participant is approximately 10 weeks, and due to the two-cohort design, there is a possibility of additional waiting time. Outcome assessments will be conducted at two main time points: at baseline (T0), before randomisation and prior to the first intervention session, and at post-intervention (T2), in the week following completion of the 8-week programme. In both groups, adherence to the intervention and adverse events will be monitored from week 0 (T1) onwards and evaluated every 2 weeks during the 8-week period at weeks 2, 4, 6 and 8 as shown in figure 1. Participant flow diagram is detailed in table 2.

**Figure 1 F1:**
[figure not shown]
Participant flow diagram.

**Table 2 T2:** Participant timeline: Schedule of enrolment, assessments and interventions

	Trial period		
	Enrolment/ baseline measurement	Initiation of the interventions Week 0	Post-intervention measurement Week 8
Timepoint	T_0_	T_1_	T_2_*
Enrolment:			
Eligibility criteria Phone-screening	X†		
Informed consent	X†		
Sociodemographic and clinical history	X†		
Invitation to the study centre	X†		
Inclusion/exclusion criteria	X ‡		
Diagnostic confirmation	X ‡		
Official inclusion of participants	X ‡		
Randomisation	X ‡		
Assessments:			
Fibromyalgia Impact Questionnaire (FIQ)	X‡		X
Central Sensitisation Inventory (CSI)	X‡		X
Heart Rate Variability (HRV)	X‡		X
Visual Analogue Scale (VAS)	X‡		X
Multidimensional Fatigue Index (MFI-20)	X‡		X
Pittsburgh Sleep Quality Index (PSQI)	X‡		X
Perceived Stress Scale (PSS)	X‡		X
Adverse events		X§ 	X§
Adherence		X§ 	X§
Intervention/comparator:			
Intervention¶		X 	X
Comparator**		X 	X

* Second measurement appointment at study centre.

† Before the first appointment.

‡ First appointment at study centre.

§ Adverse events and adherence (continuous monitoring; exercise diary review at weeks 2/4/6/8 covering the preceding interval).

¶ PhYoMind intervention (physiotherapy techniques+yoga+mindfulness) and home exercise programme.

** Only home exercise programme.

### Sample size estimation

Sample size was estimated using G*Power (V.3.1.9.7; Franz Foul, University of Kiel, Germany). The sample size was calculated based on a Repeated Measures Analysis of Variance (ANOVA), according to effect estimates from previous studies using our primary outcome, the Revised Fibromyalgia Impact Questionnaire.^57^ A minimum total number of participants of 32 is required to achieve 95% power with a type I error of α=0.05, for an expected effect size f=0.675 (d=1.35). Taking into account an expected dropout rate of 20%, the required sample size for our study is 40 participants, with 20 individuals per group.

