**Methods and analysis:**

This monocentric study uses a parallel-group (1:1) randomised controlled design, in which the outcome assessor and statistician are blinded to group allocation. Individuals with a clinical diagnosis of FMS (n=40) will be included in the study (Cohen’s f=0.675; α=0.05; power=0.80). Participants will be randomised to receive either PYM intervention in addition to Home Exercise (HE) programme or HE programme alone. The intervention period for both groups will last 8 weeks; PYM sessions will be held twice a week for 75 min each. The primary outcome is the broad disease impact and functional impairments measured by the total score of the Fibromyalgia Impact Questionnaire. Secondary outcomes include central sensitivity, as assessed by the Central Sensitisation Index; autonomic nervous system function, as measured objectively by heart rate variability; pain perception (current, average, worst), as assessed by the Visual Analogue Scale; fatigue, as assessed by the Multidimensional Fatigue Inventory; stress, as assessed by the Perceived Stress Scale; and sleep quality as assessed by the Pittsburgh Sleep Quality Index. Adherence and adverse events will be assessed for both interventions. Repeated measures ANOVA will be used to analyse the effect of time, intervention group and their interaction on primary and secondary outcomes under an intention-to-treat principle.

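### The abstract gives power 0.80 and the sample-size section 95% for the same effect size and alpha; the 0.80 fits neither 32 nor 40 participants and should be corrected

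*Protocol article*

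**What the plan says.** The abstract, under Methods and analysis, justifies the 40 participants in one parenthesis: "f=0.675; α=0.05; power=0.80". It mentions neither 32 evaluable participants nor dropout.

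The section Sample size estimation gives the fuller account. It names the method ("The sample size was calculated based on a Repeated Measures Analysis of Variance (ANOVA", run in G*Power) and states "A minimum total number of participants of 32 is required to achieve 95% power with a type I error of α=0.05". The effect assumed there is f = 0.675, which it equates to d = 1.35. It then allows for 20% attrition and concludes that "the required sample size for our study is 40 participants, with 20 individuals per group".

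The effect size, the alpha and the final 40 are the same in both places. Only the power differs. Both statements are current text, and nothing in the article reconciles them.

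**The concern.** Once the test, effect size, alpha and number of participants are fixed, the power is fixed too. A trial of this size cannot have both 80% and 95% power at f=0.675, so at least one figure in the justification of the sample size is wrong.

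What is at stake is the accuracy of that justification. The abstract is the part most often read and copied. As it stands, it suggests that 40 participants are what 80% power at this effect requires, and a trial report could carry the wrong figure forward. The conduct of the trial does not depend on it.

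**Working it through.** **Inputs.** From Sample size estimation: f = 0.675, d = 1.35 (consistent, since d = 2f for two equal groups), alpha = 0.05, power 95%, N = 32 evaluable, dropout 20%, 40 randomised at 20 per group. From the abstract: the same f and alpha, power 0.80, n = 40.

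**Assumption.** The article does not give the sidedness of alpha, the repeated-measures option chosen in G*Power, or the correlation between the two time points. The base case is therefore a two-sided comparison of two equal groups: an F test with 1 and N − 2 degrees of freedom and noncentrality λ = f²N. This is identical to a two-sample t test at d = 1.35.

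**Step 1: reproduce the figures in the sample-size section.** f² = 0.675² = 0.4556.

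| N (total) | λ = 0.4556 × N | Power |
|---|---|---|
| 18 | 8.20 | 76.7% |
| 20 | 9.11 | 81.4% |
| 30 | 13.67 | 94.6% |
| 32 | 14.58 | 95.9% |
| 40 | 18.23 | 98.6% |

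The smallest even N with at least 95% power is 32. Dropout: 32 / (1 − 0.20) = 40. Both figures reproduce.

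**Step 2: test the abstract's 0.80.** The smallest even N with at least 80% power is 20. With 20% dropout, 20 / 0.80 = 25, or 26 for equal groups. At the numbers the plan uses, power is 95.9% (32) or 98.6% (40).

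**Step 3: try other readings of the calculation.** Total N needed at f = 0.675:

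| Variant | 80% power | 95% power |
|---|---|---|
| Two-sided two-group test | 20 | 32 |
| One-sided two-group test | 16 | 26 |
| Repeated measures, between-factor, correlation 0 to 0.99 | 12 to 20 | 18 to 32 |
| Repeated measures, interaction, correlation 0 to 0.99 | 12 or fewer | 18 or fewer |

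For two groups and two time points, the repeated-measures rows use λ = 2f²N/(1 + ρ) for the between factor and λ = 2f²N/(1 − ρ) for the interaction, where ρ is the correlation. For ρ from 0 to 0.99 both are larger than f²N, so these options need the same number or fewer. None of the variants gives 32 or 40 at 80% power.

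**The case against.** The best defence is that this is a slip in one parenthesis. The sample-size section is internally coherent, 40 follows from its inputs, and the stray figure understates the power. All of that stands, and it limits the point to a correction of text.

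A second defence is that 0.80 might be the power left after attrition. It is not: 20% dropout from 40 leaves 32, which still gives 95.9%. Nor does condensing a protocol into an article explain it, since that can drop detail but does not turn 95% into 0.80.

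A third objection is that the check uses a simple two-group test, whereas the article names repeated measures ANOVA. This is fair as regards the exact percentages. Under the between-factor option with correlation 0.5, for example, 32 participants would have 98.9% power. It does not rescue the 0.80, because every repeated-measures variant moves the power at 32 further above 80%.

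A reader might infer something stronger: that the conflict hides a lack of sensitivity, so that a null result would be misread. The documents do not support this. The abstract prints its effect size beside the power, and at that effect the true power is higher than stated. Limited power for effects well below d = 1.35 comes from planning on a large effect, and would be the same if both places said 95%. How a null result will be interpreted, and which SD the d refers to, are separate questions that this conflict does not settle.

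**Conclusion.** The point holds as an error of reporting. The abstract's 0.80 is incompatible with the sample-size section's 95%, and the recalculation shows that the abstract is the one to change. Under the base-case assumption the gap at f = 0.675 is 80% stated against 95.9% with 32 evaluable, or 98.6% if all 40 are evaluable. Put in numbers of participants, 80% power needs 20 evaluable, not 32.

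The conclusion that 0.80 fits neither 32 nor 40 holds under every variant tried. The exact percentages hold only for the two-sided two-group comparison. The error understates the power at the assumed effect and gives no reason to change the sample size or the analysis.

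**What to change.** Change the parenthesis in the abstract to read, for example: *32 evaluable participants give 95% power for f=0.675 (d=1.35) at alpha=0.05; 40 randomised to allow for 20% dropout.* The abstract and the section Sample size estimation then state one power. If the 0.80 has been carried into other trial documents, correct it there too.

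Optionally, the authors could add the effect detectable with 80% power: about d = 1.02 with 32 evaluable and d = 0.91 with 40. These figures must be labelled as assuming a simple two-group comparison, because they do not describe the repeated measures ANOVA that the article names.

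The cost is a text correction. It needs no further participants and no change to design or analysis.

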### Randomisation and blinding

The block randomisation method with randomly varying block sizes between 2 and 8^58^ will be used to ensure an unbiased and random allocation of participants into the two treatment groups: Intervention group and control group (1:1). A study team member ([name]) who is not involved in participant recruitment, outcome assessment or intervention delivery generated the random allocation sequence using the R statistical software (V.4.5.0, R Core Team 2025) and the package *blockrand*, V.1.5.^59^ The full randomisation list is stored in a secure file inaccessible to study team members responsible for enrolment, assessment or intervention delivery. Immediately after baseline measurement, randomisation will be carried out using the REDCap system^60 61^ and participants will then be informed of their group allocation prior to the first intervention appointment.

The outcome assessor as well as the statistician performing the data analysis will be blinded to group allocation. Due to the nature of the interventions, participants and the study physician delivering the PYM sessions cannot be blinded.

To maintain blinding, group labels will be coded (eg, Group A/Group B) in the dataset that will be provided to the statistician, and outcome assessments will be scheduled and conducted separately from the intervention sessions. Participants will be requested not to disclose details of their assigned intervention during assessments, and outcome assessors will be instructed not to ask about group allocation. Unblinding of the outcome assessor or statistician will occur only in exceptional circumstances when knowledge of treatment allocation is essential for participant safety. The principal investigator will request unblinding from the data manager (who holds the allocation file), if it’s necessary and the reason and timing will be documented.

### Data collection and management

Outcome measurements will be carried out before and after the 8-week programme; adverse effects and adherence will be monitored every 2 weeks. Data collection and all validated questionnaires will be administered by the outcome assessors: Baseline eligibility and ACR-criteria confirmation will be performed by [name], a study physician; and ([name]), a physiotherapist and doctoral researcher who will conduct the primary and secondary outcome assessments at both baseline and post-intervention. Assessments will take place at baseline and at week 8 of the study which includes the confirmation of eligibility/visit procedures, HRV measurement and completion of questionnaires. To ensure consistency across participants and visits, a structured assessment procedure will be employed, encompassing both written instructions and a checklist. For example, instructions regarding points to keep in mind regarding the HRV prior to the measurement appointment will be provided to participants via email and telephone (eg, avoiding alcohol/coffee, smoking, intense exercise and heavy meals before HRV assessment). A checklist will be prepared containing instructions for the outcome assessor to follow, written in the same order and using the same wording during the measurements. Participants will primarily complete questionnaires electronically on tablet via REDCap; paper forms will be available if required and entered into REDCap by the outcome assessors. HRV measurements will be recorded under standardised conditions (quiet room, seated position, after a brief rest) and stored in REDCap. Should any artefacts requiring more than 5% correction be detected, whether due to unintended movement or speech during HRV measurement, the procedure will be repeated. To promote data quality and ensure higher adherence, appointments will be scheduled flexibly, reminder calls or e-mails will be used when necessary, and a contact person will be available during the study. For participants who discontinue or deviate from the intervention protocols, all feasible outcome data at week 8 will be collected, provided that informed consent is maintained.

Only anonymised results will be reported, and study data will be retained for up to 10 years in line with institutional and legal requirements before being deleted or irreversibly anonymised. Participants may withdraw their consent at any time without disadvantage. No further data will then be collected, but any pseudonymised data already collected may continue to be used for analysis, unless patients explicitly request their deletion.

The study team will monitor the conduct of the study, participant recruitment, informed consent procedures, protocol compliance, adverse events and data integrity through regular internal reviews. Monitoring will be carried out continuously throughout the study, and a formal review will take place at regular study team meetings. As this is a monocentric, low-risk, non-pharmacological study, no separate external monitoring body has been established.

### Statistical analysis

The data obtained during the study will be analysed using the statistical software R, V.R-4.3.3 for Windows. Descriptive statistics including mean, SD, median, etc, will be calculated for demographic and clinical characteristics in both groups. Repeated Measures ANOVA (rmANOVA) will be used to analyse the effect of time, intervention group and their interaction on primary and secondary outcomes. Time will be considered as the within-subject factor and group will be considered as the between-subject factor. Effect sizes and group differences will be reported subsequently. The significance level will be p<0.05.

To ensure the robustness and validity of the statistical analysis, missing data will be addressed using multiple imputation. All randomised participants will be included in the main analyses according to the intention-to-treat principle and will be analysed in the groups to which they were originally allocated. Serious and non-serious adverse events and drop-outs during the intervention period will be summarised and compared between groups using absolute and relative frequencies. Given the relatively limited sample size, no formal mediation analysis is planned as part of the confirmatory or secondary statistical analyses. Associations between fibromyalgia severity, perceived stress and clinical outcomes may be explored descriptively or in exploratory regression models, but these analyses will be considered hypothesis-generating and interpreted with caution. No formal interim analyses are planned, and no predefined stopping rules for efficacy or futility have been established.

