PYM intervention stands out for its unique approach to addressing FMS symptoms; this programme, in which the techniques used in physiotherapy, yoga and mindfulness components are presented as a cohesive whole rather than as discrete modules, represents a distinctive within an integrated, replicable programme. Beyond this, the fact that the intervention group carries out both PYM and HEs has the potential to yield greater synergistic benefits for the intervention group. To the best of our knowledge, no existing research has examined the effect of integrating certain physiotherapy techniques with yoga and mindfulness in FMS patients, as proposed in this study. Therefore, the primary objective of this trial is to evaluate whether an 8-week PYM intervention in addition to HEs is superior to HEs alone in improving fibromyalgia symptom severity and functional impact after the intervention in adults with FMS. Secondary objectives are to compare the effects of the PYM and HE combination on central sensitivity, autonomic nervous system function, pain perception, perceived stress, fatigue and sleep quality with those of HEs alone. Furthermore, the study aims to monitor adverse events to assess the safety of both interventions and evaluate adherence and attendance as feasibility outcomes.

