### Outcomes

As a primary outcome, the Fibromyalgia Impact Questionnaire (FIQ) will be used to assess participants’ functional disability before and after the intervention.^46^ The FIQ is a valid and reliable questionnaire with a total score ranging between 0–100 and measuring overall impact, including symptom severity, functionality, work difficulties, morning fatigue, depression, anxiety and general well-being rated by individuals with fibromyalgia. Higher scores indicate a greater impact of symptoms.^47^

Secondary outcomes will be measured using the following tools, with the following parameters being collected: Central Sensitisation Inventory (CSI),^48^ 20-item Multidimensional Fatigue Index (MFI-20),^49 50^ Pittsburgh Sleep Quality Index (PSQI),^51^ Perceived Stress Scale (PSS)^52^ and Visual Analogue Scale (VAS) for current, average and worst pain intensity of the participants over the last week.^53^

As a secondary outcome, changes in the autonomic nervous system will also be objectively recorded by measuring HRV. It will be measured and recorded with a Polar H10 (Polar Electro UK, Warwick, UK) chest strap using the validated Elite HRV mobile application, which has ease of use, reliability, data recording, storage, analysis and export features.^54^,^56^ The Polar H10 chest strap is CE certified and meets the EU requirements for non-invasive physiological data measurements. Participants will be requested to sit in silence for a period of 5 min, after which a 5-minute recording will be made for the purpose of analysis. During the HRV recording, participants will remain seated and quiet, with no physical activity. Breathing rate and depth will not be controlled. With the Polar H10 chest strap device, minimum-maximum-average Heart Rate (HR), HRV parameters: RMSSD (Square Root of the Mean of the Sum of the Squares of the Differences between RR Intervals), SDNN (Mean and SD of RR Intervals), total power, mean R-R interval, HF (High Frequency), LF (Low Frequency), LF/HF, (with their log-transformed indices lnRMSSD, lnHF, lnLF) will be collected and recorded in the Elite HRV application and manually entered into REDCap system.

Further assessments, as part of the initial measurement and questionnaire administration, demographic data of the participants will be collected. These data include age, sex, marital status, educational status, working status, duration of fibromyalgia and any relevant health conditions (other than exclusion criteria).

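### The two-visit rmANOVA names no confirmatory term, and its one relevant term, the group-by-time interaction, is valid but usually less precise than a baseline-adjusted ANCOVA

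*Protocol article*

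**What the plan says.** The Statistical analysis section fixes the model: "Repeated Measures ANOVA (rmANOVA) will be used to analyse the effect of time, intervention group and their interaction on primary and secondary outcomes". It then fixes the factors: "Time will be considered as the within-subject factor and group will be considered as the between-subject factor". The level follows: "The significance level will be p<0.05". The Abstract repeats the three effects: "to analyse the effect of time, intervention group and their interaction on primary and secondary outcomes under an intention-to-treat principle". Neither place says which effect is the confirmatory one, and neither names a baseline covariate.

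The design has two outcome visits. Participants timeline: "Outcome assessments will be conducted at two main time points: at baseline (T0), before randomisation and prior to the first intervention session", and then T2 in the week after the 8-week programme. Outcomes, on the primary measure: "the Fibromyalgia Impact Questionnaire (FIQ) will be used to assess participants’ functional disability before and after the intervention".

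The objective at the end of the Introduction is a single between-group question, whether PYM plus home exercise "is superior to HEs alone in improving fibromyalgia symptom severity and functional impact after the intervention in adults with FMS".

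**The concern.** With one baseline and one post-treatment score, the three listed effects answer three different questions.

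- **Time** is the average change over both arms. It does not compare treatments. Both arms do the home exercise programme, so a time effect could appear even if PYM adds nothing.
- **Group** is the difference between arms in the mean of T0 and T2. T0 precedes randomisation, so treatment cannot affect it, and the term is diluted.
- **Group by time** is the difference between arms in change. Only this term matches the objective.

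Two things are at stake. First, the plan lists three effects at one level without saying which one decides the trial. Second, the relevant term fixes the weight of the baseline score at 1, whereas ANCOVA estimates that weight. In a trial of 32 to 40 people this can lose precision that the collected data could provide.

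**Working it through.** **Inputs.** From Sample size estimation: f=0.675, d=1.35, N=32 for 95% power, 20% dropout, 40 randomised. From Statistical analysis: level 0.05. Assumed, because the documents do not give them: the T0-to-T2 correlation r, equal SDs at both visits, and d expressed on the raw FIQ SD.

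**Step 1: the stated N.** "A minimum total number of participants of 32 is required to achieve 95% power with a type I error of α=0.05". A plain two-group F test has noncentrality λ = N·f² = 32 × 0.675² = 14.58 on 1 and 30 df, which gives power 0.9585. Then 32/0.80 = 40. Both stated numbers reproduce.

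**Step 2: what each contrast estimates.** Scale the SD to 1 at both visits, with a treatment effect d at T2 only.

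- Interaction (T2 − T0): difference d, variance per person 2(1−r).
- Group main effect ((T0 + T2)/2): difference d/2, variance (1+r)/2.
- ANCOVA: difference d, variance (1−r²), multiplied by 1 + 1/(N−4) for estimating the slope.

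For the interaction, λ = N·d²/[4 × 2(1−r)] = 32 × 1.8225/[8(1−r)] = 7.29/(1−r). This equals the 14.58 of step 1 only at r=0.5.

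**Step 3: variance, ANCOVA relative to interaction.** The ratio is (1−r²)/[2(1−r)] × [1 + 1/(N−4)] = (1+r)/2 × [1 + 1/(N−4)]. Example at r=0.5, N=32: 0.75 × 29/28 = 0.777, a reduction of 22%.

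| Assumed r | Large sample, (1−r)/2 | N=32 | N=40 |
|---|---|---|---|
| 0.3 | 35% | 33% | 33% |
| 0.5 | 25% | 22% | 23% |
| 0.7 | 15% | 12% | 13% |
| 0.8 | 10% | 7% | 7.5% |
| 0.9 | 5% | 2% | 2.4% |

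At N=32 the gain disappears where (1+r)/2 = 28/29, that is r = 27/29 ≈ 0.93. A simulation at N=32 (40,000 trials per value of r) gave reductions of 33.1%, 22.7% and 12.3% at r = 0.3, 0.5 and 0.7.

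**Step 4: power at N=32.** The value d=0.8 is an assumption, used to show a smaller true effect.

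| Assumed r | d=1.35: interaction | d=1.35: ANCOVA | d=1.35: group main effect | d=0.8: interaction | d=0.8: ANCOVA |
|---|---|---|---|---|---|
| 0.3 | 0.88 | 0.97 | 0.63 | 0.46 | 0.62 |
| 0.5 | 0.96 | 0.99 | 0.57 | 0.59 | 0.70 |
| 0.7 | 0.997 | 0.999 | 0.52 | 0.81 | 0.85 |

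If all 40 participants complete, the d=1.35, r=0.3 comparison is 0.94 vs 0.99.

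**Step 5: validity.** In the same simulation under no effect, the interaction rejected in 4.9 to 5.1% of trials and ANCOVA in 4.8 to 5.0%. If a significant group effect or a significant interaction were each taken as success, the null error would be about 1 − 0.95² = 9.75% (simulated 9.6 to 9.8%).

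**The case against.** The strongest reply is that the plan already contains a correct test. The two-visit interaction is a change-score t-test, which is unbiased under randomisation and holds its level. Regression to the mean affects both arms equally in expectation, so it costs efficiency and does not bias the comparison. This stands: a reader might infer that the rmANOVA is invalid and that ANCOVA is the only correct test, and step 5 shows otherwise.

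A reader might also infer that testing three effects at 0.05 doubles the type I error. The protocol does not say that a group or time main effect would count as success. It states one superiority objective and one primary outcome, and listing the three effects is the ordinary description of an rmANOVA. The figure of about 10% is therefore conditional on a misreading that the text leaves open but does not plan.

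The size of the gain is also uncertain. A flat claim of 15 to 35% less variance would rest on an assumed r of 0.3 to 0.7 and on large-sample variances. At r of 0.8 or more the gain at N=32 is about 7% or less. At d=1.35 the interaction already meets 95% power for r of 0.5 or more, so a shortfall against the stated power appears only at low r.

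Finally, the confirmatory contrast may be named in an analysis plan that is not shown. That is a fair defence of the silence about which term decides. It does not cover the choice of model, which the article itself fixes along with the factors and the level.

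**Conclusion.** The point holds as a matter of efficiency and clarity, not as an error in validity. The article commits to a model with three effects, of which only the interaction addresses the objective, and does not say so. The group main effect targets half the treatment effect and has power of only 0.52 to 0.63 at the planned d for r of 0.7 to 0.3.

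Baseline-adjusted ANCOVA answers the same question with a smaller variance over most of the plausible range: about 33% less at r=0.3, down to 2% less at r=0.9, with N=32. At d=1.35 this matters mainly when r is low. At a smaller true effect it matters more: at d=0.8, the gain is 16 percentage points at r=0.3 (0.46 to 0.62) and 11 at r=0.5 (0.59 to 0.70). All these sizes depend on the assumed r, equal variances and d on the raw SD. The change is advisable because it is nearly free, but the planned interaction test would not make the trial's result wrong.

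**What to change.** Before unblinding, state one confirmatory test: the adjusted difference between allocated groups in T2 FIQ total score, with 95% CI, from a linear model with allocated group and baseline FIQ. Use the same model for each secondary outcome with that outcome's own baseline value. Report rmANOVA time and group effects descriptively only. The planned multiple imputation and intention-to-treat set can stay as they are.

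The cost is one degree of freedom and a change of wording in the protocol and any analysis plan, with no new data or visits. Methods and design says that recruitment has begun, so the change should be dated and its timing relative to unblinding recorded. If the sponsor prefers to keep the rmANOVA, the minimum is to name the group-by-time interaction as the only confirmatory term.
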